##### Ophthalmological assessment

2.4.3.2

Visual evoked potential that measures the electrical conductivity is performed by a technologist at the CTC and supervised by the leading neurologist at the Jordan University Hospital.

Optical coherence tomography is conducted by technologist and supervised by an ophthalmologist at the Jordan University Hospital. A measurement of the retinal nerve fiber layer in um and comparison to the baseline measurements in both the poor eye and less affected eye would indicate the outcome of the Optical coherence tomography examination. While the increase or decrease in the speed of electrical conduction in milliseconds of the nerve fiber would be evaluated as the target heart rate range outcomes.

##### Radiological Assessment

2.4.3.3

T2-weighted FLAIR and T1-weighted MPRAGE images are generated for all patients. The detailed imaging sequences protocol of the brain and those of the cervical and thoracic spine have been previously described.^[11]^ Fuzzy connections algorithm in JIM software is used to calculate lesion volume measurements.^[57]^

*2.4.3.5. MRI scanning* is performed at Farah hospital using a 3 Tesla (3T) imaging device to measure lesion load. Scheduling the MRI scanning will be on a separate occasion within 7 days from the day of the baseline assessment and prior to receiving the treatment.

### Participant timeline

2.5

Eligible participants will be scheduled for their baseline assessments. They will undergo a comprehensive battery of measures including motor, non-motor, and medical assessments, which will take around 2 to 3 hours to complete. Part of the baseline assessment that include MRI imaging will be performed on another day within a week from the baseline assessment on a time convenient to the participant. Participants will repeat these measures at 3, 6, and 12 months post the baseline assessment (Fig. 1).

### Allocation

2.6

Participants will be randomly allocated to 1 of 3 groups using a computer-generated software.

### Blinding

2.7

This study is single-blinded where the researchers involved in the assessments are blinded to the allocation of the participants to each group.

### Data management and confidentiality

2.8

All members of the research team work to protect the privacy of participants and the confidentiality of data. Personal identifiers are limited only on data collection hard copy forms and all data files are kept in a locked file cabinet. Each participant is given a unique identifier (symbol and number) and their electronic data is stored in university network drives and data collection occurs on an encrypted password-protected laptop computer. Data is available and accessed only by the study research personnel.

### Statistical analysis

2.9

Statistical Package for the Social Sciences (SPSS) 23.0 (SPSS: Inc., Chicago, IL, USA) will be used to perform all statistical analysis and alpha is set at 0.05. Correlations will be utilized to assess the relationship between the outcome measures of interest. Changes in outcomes at the follow-up scores for within-group and between-group differences will be computed using analysis of variance. Effect sizes of all outcomes will be also computed based on the difference in the change score from base line to follow up.

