### Objective

1.1

The purpose of this study is to explore the effect of PTE and WJ-MSCs injection versus PTE alone or WJ-MSCs alone on motor and non-motor symptoms in PwMS. We hypothesize that PwMS who receive the combined treatment of WJ-MSCs and PTE will demonstrate significant improvements on motor and non-motor symptoms compared to those who receive either WJ-MSCs alone or PTE alone.

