### Trial design

1.2

The proposed study utilizes a randomized controlled design to examine the combined effect of a 6-month program on motor and non-motor symptoms in PwMS. This study is single-blinded where the researchers involved in the assessments are blinded to the allocation of the participants to each group. We aim to recruit 60 participants with MS (20 in each group) that will be randomly allocated to 1 of 3 groups using a computer-generated software to either a combined treatment group (PTE + WJ-MSCs), PTE alone control group or WJ-MSCs alone control group after going through a battery of comprehensive assessments (Fig. 1).

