## Discussion

3

In this study we will investigate the combined effect of stem cell therapy and physical therapy exercises in a wide range of MS symptoms. Moreover, we will compare the effect of a combined therapy to the separate effect of each therapeutic intervention alone. This will help health care professionals dealing with PwMS to have a better understanding of the combined versus separate effects of each therapeutic intervention. The outcomes from this study may help in reducing the cost associated with the life-time care of these individuals worldwide. More importantly, this study may help improving patients’ QOL and reducing their disability. For rehabilitation specialists, neurologists, and regenerative medicine specialists, the outcomes of this trial would clarify the added value of the regenerative interventions with the physical therapy exercise on different symptoms that PwMS suffer from. This will allow them to have a better understanding of this combination to answer PwMS questions that they usually have. Moreover, the combination between biological interventions and having the patients physically active through regular and progressive exercises would emphasize the benefits that the patients may get from both techniques. The expected benefits from both interventions could lead to a medical breakthrough in the treatment of PwMS. This would have positive socio-economic impact, including reducing the treatment cost related to the chronic nature of the disease and getting this active segment of the society back to the work market.

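### Section 2.9 does not tie its ANOVA to the two comparisons in the hypothesis, so a significant F or within-group change could be read as a benefit of the combination when it adds nothing to the better single treatment

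*Protocol article*

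**What the plan says.** Section 1.1 (Objective) predicts that people given the combination "will demonstrate significant improvements on motor and non-motor symptoms compared to those who receive either WJ-MSCs alone or PTE alone". The Discussion repeats the aim: "we will compare the effect of a combined therapy to the separate effect of each therapeutic intervention alone". Section 1.2 (Trial design) allocates to "either a combined treatment group (PTE + WJ-MSCs), PTE alone control group or WJ-MSCs alone control group", with 20 planned in each group and 60 in all.

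Section 2.9 (Statistical analysis) holds the whole inferential plan. It states that "alpha is set at 0.05" and that "Changes in outcomes at the follow-up scores for within-group and between-group differences will be computed using analysis of variance". It adds correlations between outcomes and a descriptive measure: "Effect sizes of all outcomes will be also computed based on the difference in the change score from base line to follow up". No contrast between the combined arm and a single-treatment arm is named. Nothing says whether one or both comparisons must succeed. Section 2.5 has measures repeated at 3, 6 and 12 months, and none of these is designated for the hypothesis.

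**The concern.** The hypothesis consists of two directed comparisons. A one-way ANOVA over three arms asks a different question, namely whether any of the three means differ. It rejects if exercise works and cells add nothing, if cells work and exercise adds nothing, or if the combination is worse than both components.

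Section 2.9 also puts within-group change on the same footing as between-group differences. All three arms are actively treated and only the assessors are blinded. Change within the combined arm therefore mixes any treatment effect with practice on repeated tests (Stroop, symbol digit, 9-hole peg), expectation and natural course. A finding that is significant in the combined arm and not in another arm is not a comparison of arms.

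At stake is the trial's main conclusion. As written, the plan does not stop either kind of result from being reported as an advantage of the combination.

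**Working it through.** **The plan's own figure.** 3 × 20 = 60, which agrees. No power, target effect or SD is given, so the sample size cannot be reproduced further.

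**Inputs.** From the protocol: three arms, n = 20 per arm, alpha 0.05. Assumed: two-sided tests, normal change scores with equal variance, no dropout, effects in SD of the change score.

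**1. Omnibus F.** Let the combined arm equal one single treatment, with the other lower by d. The means are (0, 0, −d), the grand mean is −d/3, and the sum of squared deviations is 2(d/3)² + (2d/3)² = 2d²/3. The noncentrality is λ = 20 × 2d²/3 = 13.33d². The critical F on 2 and 57 df is 3.159.

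**2. Both contrasts required.** Each contrast is t = (combined mean − single mean) / √(2s²/20) on 57 df, with critical value 2.002. Both must favour the combination. One of the contrasts is truly null here, so the joint rate cannot exceed 0.025.

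| d (SD) | λ | F significant | Both contrasts significant | F, then both pairwise tests significant |
|---|---|---|---|---|
| 0.5 | 3.33 | 34% | 2.1% | 2.0% |
| 0.8 | 8.53 | 72% | 2.4–2.5% | 2.4–2.5% |
| 1.0 | 13.33 | 90% | 2.4–2.5% | 2.4–2.5% |

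The F column is from the noncentral F distribution. The last two columns are from simulations of at least 100,000 trials per row. If the combination is worse than both components by 0.8 SD, λ is again 8.53 and F is significant in 72% of trials. If all arms are equal, F keeps its 5% level.

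**3. Within-group change.** For a mean change of m SD in one arm, the noncentrality is m√20. If all arms improve equally by 0.5 or 0.8 SD, the combined arm's change is significant in 57% or 92% of trials, while the between-group F stays at 5%.

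**4. Discordant within-group results.** Assume a correlation of 0.7 between baseline and follow-up. The SD of change is then √(2 × 0.3) = 0.775 baseline SD. With q the chance that one arm is significant, the chance that the combined arm is significant and at least one other arm is not is q(1 − q²).

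| Same shift in every arm (baseline SD) | q | q(1 − q²) |
|---|---|---|
| 0.1 | 0.08 | 8% |
| 0.2 | 0.19 | 19% |
| 0.4 | 0.59 | 38% |
| 0.6 | 0.91 | 16% |
| 0.8 | 0.99 | under 2% |

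The maximum of q(1 − q²) is 38.5%, at q = 1/√3, so the 0.4 row sits at the peak.

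**5. Power of the both-contrasts rule.** For a true advantage over each component of 0.5, 0.8, 0.9 and 1.0 SD, power is about 19%, 56%, 69% and 80%. A single contrast at 0.9 SD has about 80%.

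**6. Claiming one contrast alone.** With all arms equal and each contrast tested at an unadjusted 0.05, at least one is significant in about 9% of trials. About half of these favour the combination.

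**The case against.** The strongest reply is that section 2.9 never says an omnibus F will decide the matter. Between-group differences computed by ANOVA can include pairwise comparisons, and sections 1.1 and 3 make clear which pairs are meant. The article is condensed, and a full protocol or analysis plan may name the contrasts. This largely stands. A reader might infer that the planned ANOVA cannot test the hypothesis, or that the trial would falsely claim superiority in 72% to 90% of cases. The document supports neither. Those percentages count F rejections, and routine pairwise tests after the F bring the false joint claim back to about 2% to 2.5%.

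Three further points stand. In the scenario tabulated, the combination really is better than one component, so a significant F is not empty of information; it fails to support superiority over both. The either–or wording in section 1.1 does not say outright that both comparisons must succeed. The within-group figures depend heavily on the assumed shift, and section 2.9 does not say that within-group results will be set against each other across arms.

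The lack of an untreated arm is no defect for this aim, which is to compare the combination with its components. It only limits what within-group change can show.

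What the reply does not remove is that the article does state an analysis, and that analysis is not tied to the hypothesis. Even if pairwise tests are intended, which pairs count and whether one or both must succeed remain open, and the second choice determines whether a multiplicity adjustment is needed.

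**Conclusion.** The point holds in a limited form. Section 2.9 leaves the test of the main hypothesis unspecified and gives within-group testing equal standing. If the three-group F is taken as the test, it is significant in about 34% to 90% of trials in which the combination only equals the better single treatment and the other is 0.5 to 1.0 SD worse. Requiring both contrasts gives 2.1% to 2.5%. If within-group change is taken as the test, an equal improvement of 0.5 to 0.8 SD in all arms makes the combined arm significant in 57% to 92% of trials.

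These sizes rest on assumed effects, normality, equal variances and complete data. They describe what the wording permits, not what the investigators will necessarily do. The F misleads only when the arms truly differ in some way other than the one hypothesised.

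**What to change.** In section 2.9, replace the ANOVA sentence with wording to this effect:

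> The hypothesis is tested by two pre-specified between-arm contrasts of change from baseline, combined minus PTE alone and combined minus WJ-MSCs alone, at [time point]. Superiority over both single treatments is claimed only if both contrasts favour the combination at two-sided 0.05. Within-group changes are reported as means with 95% confidence intervals, descriptively, and not as evidence of treatment effect.

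The sponsor must settle two things beforehand:

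- **Time point.** Six months, the end of the supervised programme, is one candidate.
- **Scope of the claim.** If only the joint claim is made, no alpha split is needed. If a claim on one contrast alone is to be allowed, apply Holm across the two, since unadjusted testing gives about 9% familywise error.

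Arms, visits and sample size do not change. The cost is power: with 20 per arm, about 69% to win both contrasts at a true advantage of 0.9 SD over each, against about 80% for either alone. The rule applies outcome by outcome and does not deal with multiplicity across the many outcomes.

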### Eligibility criteria

2.2

Interested participants will be checked for the inclusion/exclusion criteria where they will undergo a thorough neurological exam performed by a neurologist to generate the expanded disability status scale (EDSS), and a trained research personnel will perform the mini mental state examination.^[18]^ A screening form is also filled out for every participant that includes demographics, general history of the disease, past, and current medication intake and relevant clinical aspects of the disease. Participants will be selected based on the following eligibility criteria:

Inclusion criteria:

(1)Males and females.(2)Eighteen years and older.(3)Written informed consent prior participation.(4)Independent in ambulation even with the use of an assistive device.(5)All types of MS.(6)EDSS score < 6.5.(7)mini mental state examination score ≥ 24.

Exclusion criteria:

(1)Uncorrected vision loss.(2)History of a nervous system disorder other than MS.(3)Severe physical, neurological, or sensory impairments that would interfere significantly with testing.(4)Developmental history of learning disability or attention-deficit/hyperactivity disorder.(5)Relapse and/or corticosteroid use within 4 weeks of assessment.(6)Acute ischemic cardiovascular event or coronary artery bypass surgery less than 3 months.(7)Uncontrolled blood pressure with medication (blood pressure (BP) > 190/110 mm Hg).

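### ANOVA on change from baseline, instead of adjustment for the baseline value, gives up precision that a trial with 20 per arm could have almost for free

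*Protocol article*

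**What the plan says.** Section 2.9 of the protocol article names the method: "Changes in outcomes at the follow-up scores for within-group and between-group differences will be computed using analysis of variance". It continues: "Effect sizes of all outcomes will be also computed based on the difference in the change score from base line to follow up". The software is "Statistical Package for the Social Sciences (SPSS) 23.0" and "alpha is set at 0.05". No covariate, mixed model or denominator for the effect size is named.

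The trial plans 60 participants, 20 in each of three arms (Trial design, 1.2). On timing, the Participant timeline (2.5) says: "Participants will repeat these measures at 3, 6, and 12 months post the baseline assessment". Each outcome therefore has one baseline and three follow-up values.

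**The concern.** The trial compares the combination with each single active treatment, at 20 per arm, so precision is scarce. Entry is broad: adults of any age, EDSS below 6.5 and "All types of MS". Baseline scores will therefore vary widely, and some chance imbalance between arms is to be expected.

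A change score subtracts the whole baseline value. When r is below 1 that is generally too much, and the excess adds noise to the contrast. A model that estimates the slope on baseline removes that noise with data already collected. At stake are wider intervals and lower power than the same 60 participants could give, plus a possible further loss from missed visits that depends on how the ANOVA is run.

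**Working it through.** **Inputs from the article.** 20 per arm and 60 in total (1.2); three follow-up visits (2.5); alpha 0.05 (2.9), taken here as two-sided.

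**Assumptions.** The article gives no correlation, SD, target effect or missed-visit rate. I take r from 0.5 to 0.9, equal SD s at baseline and follow-up, an illustrative effect of 0.8 s, and 5% to 15% missed per follow-up visit.

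**What 20 per arm detects.** The article states no effect or power, so there is no sample-size calculation to reproduce. Working backwards by normal approximation, 80% power needs a pairwise difference of (1.960 + 0.842) × sqrt(2/20) = 0.89 SD of whatever score is analysed.

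**Variance per participant.**
- Change score: 2s²(1−r).
- Baseline-adjusted: s²(1−r²).
- Ratio, adjusted to change: (1−r²)/[2(1−r)] = (1+r)/2.

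Estimating the common slope inflates the adjusted variance by about 1 + 1/(60−3−2) = 1 + 1/55 = 1.018. Power below is from the noncentral t, with 57 df for change and 56 df for adjustment, and includes that inflation.

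| r | (1+r)/2 | after slope cost | 20/[(1+r)/2] per arm | power, change | power, adjusted |
|---|---|---|---|---|---|
| 0.5 | 0.75 | 0.76 | 26.7 | 0.70 | 0.81 |
| 0.7 | 0.85 | 0.87 | 23.5 | 0.89 | 0.93 |
| 0.8 | 0.90 | 0.92 | 22.2 | 0.98 | 0.98 |
| 0.9 | 0.95 | 0.97 | 21.1 | 1.00 | 1.00 |

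**Dependence on equal SDs.** If the follow-up SD is k times the baseline SD, change variance minus adjusted variance is s²[(1 + k² − 2kr) − k²(1−r²)] = s²(1−kr)². This is never negative, so apart from the slope cost adjustment cannot do worse.

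**Missed visits, only if all visits enter one repeated-measures GLM.** This keeps complete cases: 60 × (1−m)³ for an independent miss rate m at each of three visits.
- m = 5%: 60 × 0.857 = 51.4
- m = 10%: 60 × 0.729 = 43.7
- m = 15%: 60 × 0.614 = 36.8

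A simulation of 3,000 trials (equal correlation between visits, effect 0.8 s, 10% missed per visit) gave this power for the 12-month contrast:

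| r | change, complete cases | change, all with month 12 | adjusted, all with month 12 |
|---|---|---|---|
| 0.5 | 0.55 | 0.64 | 0.76 |
| 0.7 | 0.77 | 0.86 | 0.91 |

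The step from the first to the second column arises only under the repeated-measures reading. The step from the second to the third arises under either reading.

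**The case against.** Four stronger readings are tempting, and the article supports none of them.

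- **That the baseline is thrown away, or the comparison biased.** Change scores use the baseline, with slope 1, and are unbiased under randomisation. A chance baseline difference d does shift a given contrast by −(1−r)d, but averaged over randomisations that shift is exactly the variance excess already counted: 2(1−r) = (1−r²) + (1−r)². Listing it as a second harm would count it twice.
- **That participants with a missed visit will be excluded.** Section 2.9 says only analysis of variance. Separate ANOVAs per visit would lose only those absent at that visit. The retention figures also assume independent misses. With dropout alone, 10% to 20% lost by month 12 leaves 54 to 48 of 60, and the approaches differ less.
- **That the effect sizes are distorted.** Dividing by the SD of change would multiply them by 1/sqrt(2(1−r)) relative to the baseline SD: 1.00 at r = 0.5, 1.29 at 0.7 and 1.58 at 0.8. But the article names only the numerator, and that fits a baseline-SD denominator equally well.
- **That covariates are ruled out.** They are not mentioned, and an analysis plan not shown could add them.

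It can also fairly be said that the gain rests on an unknown r and nearly vanishes for very stable scales. That stands, and it limits the size of the point. What does not fall away is that the article goes beyond silence: it names ANOVA on changes as the method, and a better one is available from the same data.

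**Conclusion.** The point holds as a matter of efficiency, not validity. As stated, the analysis is unbiased but less precise than baseline adjustment. The variance reduction is about 25% at r = 0.5, 15% at 0.7, 10% at 0.8 and 5% at 0.9, less about 2% of variance for estimating the slope. For an effect of 0.8 SD this is a useful gain in power at r = 0.5 (0.70 to 0.81), a modest one at 0.7 (0.89 to 0.93) and almost none at 0.8 and above. These sizes rest on assumed correlations and equal SDs.

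The complete-case loss is conditional on a repeated-measures ANOVA being meant, which the wording allows but does not say. It is a reason to choose a model that settles the question, not a demonstrated fault.

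**What to change.** In section 2.9, replace the change-score ANOVA with wording such as: for each outcome, a linear mixed model (SPSS MIXED) of the 3-, 6- and 12-month values, with arm, visit, arm-by-visit and baseline value by visit, including every participant with at least one follow-up value, in the allocated arm. Add baseline EDSS as a covariate only where EDSS is not itself the outcome; otherwise it enters twice. Report adjusted mean differences between arms with 95% confidence intervals, and standardise effect sizes by the pooled baseline SD.

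I would not add MS type as a covariate unless it is confirmed as recorded. The Eligibility criteria section (2.2) refers to disease history and clinical aspects but does not list it explicitly.

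The cost is a change of statistical wording and about one degree of freedom per covariate. The baseline values and EDSS are already collected and the named software has the procedure, so no participant, visit or measurement changes.

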### Ethics and dissemination

2.10

This trial has been approved by the Ethics Review Committee at University of Jordan. Prior to participation in the study, written informed consent will be obtained from each participant. The research personnel involved in the study will carefully explain the consent form to each participant including potential risks and benefits of study participation. Any changes to the study protocol will require approval from University of Jordan Ethics Review Board.

The results of current trial will be published in peer-reviewed journals and presented in national and international scientific meetings and conferences to promote dissemination.

